## Abstract

Radiation pneumonitis in lung cancer patients often occurs only several months after the treatment and, therefore, may be missed. Elderly lung cancer patients have a greater risk of developing radiation pneumonitis than younger patients. The present prospective multi-center trial (NCT06480734) evaluates a specific symptom-based scoring system for lung cancer in patients aged ≥65 years. It aims to identify the optimal cut-off score in order to facilitate the diagnosis of radiation pneumonitis and its discrimination from other lung diseases. In addition, patient satisfaction with the symptom-based scoring system will be assessed. The optimal cut-off score is a prerequisite for the development of a corresponding mobile application that can be used by elderly lung cancer patients at home.

## 1. Introduction

Lung cancer belongs to the most common types of solid cancer in Europe and Northern America [1]. Most patients with small cell lung cancer receive radiotherapy in combination with chemotherapy as definitive treatment [2]. Also, a considerable number of patients with advanced non-small cell lung cancer are treated with radiotherapy with or without concurrent chemotherapy [2]. Radiation pneumonitis is a possible subacute side effect of radiotherapy for lung cancer. Severe pneumonitis was reported to be fatal in approximately 2% of patients experiencing this adverse event [3].

Pneumonitis may occur up to 23 weeks following radiotherapy [4,5]. The symptoms may not be associated with the previously administered radiation treatment, and pneumonitis may be missed. Symptoms of pneumonitis generally include a cough, shortness of breath, and fever. In a previous prospective trial that included patients of any age, a scoring system was developed to contribute to a more precise and earlier detection of symptomatic radiation pneumonitis (grade ≥2) after radiotherapy for lung cancer [6]. In that trial, 0 to 3 scoring points were assigned to each of the three symptoms mentioned above. Thus, patient scores ranged between 0 and 9 points. The optimal cut-off score for the identification of pneumonitis was found to be 5 points. Moreover, an increase by 3 or more points from the baseline score was significantly associated with pneumonitis.

Since the previous trial was performed in lung cancer patients of any age, it is not clear whether its results also hold true for elderly patients aged 65 years or older [6]. This question needs to be answered to provide optimal diagnosis and treatment of pneumonitis for this growing age group. This idea is supported by the fact that several studies investigating pneumonitis after radiotherapy for lung cancer found that elderly patients had a higher risk of developing this complication [7,8,9,10,11,12,13]. In a retrospective study of our group performed in lung cancer patients aged ≥65 years, the prevalence of pneumonitis at 24 weeks following radiotherapy was 27.3% [14]. In those patients in whom the ipsilateral lung received a mean radiation dose of more than 13 Gy, the prevalence was 37.1%. For comparison, in another study, the prevalence of pneumonitis was 20.7% in patients aged ≤66 years [15].

The present prospective POLCAR trial investigates whether the results of the previous prospective trial can be generalized to elderly patients aged ≥65 years [6]. Its major goal is the identification of the optimal cut-off score to correctly diagnose pneumonitis and discriminate it from other lung diseases in elderly patients irradiated for lung cancer. In addition, the diagnostic value of an increase in the scoring points from baseline scores is evaluated. This study is a prerequisite for the development of a mobile application that can be used by patients at home to rate their symptoms possibly related to pneumonitis. This information will contribute to the decision whether pneumonitis is possible or likely and whether consultation of a pulmonologist or presentation to a hospital is required. This article reports on the study protocol of the POLCAR trial, including the objectives of the study, the eligibility criteria, planned assessments, interventions, information regarding sample size calculations, and the statistical methods used for primary and secondary outcomes.

## 2. Materials and Methods

This is a multi-center, single-arm prospective interventional study performed in two university hospitals, two academic teaching hospitals, and one private practice, which aims to establish the performance characteristics and develop a decision-algorithm of a symptom-based scoring system with respect to the identification of elderly patients developing pneumonitis after radiotherapy for lung cancer. The scoring system was created by experienced pulmonologists and successfully used in a previous trial [6].

### 2.1. Objectives and Endpoints

The primary objective is to assess the performance characteristics of the symptom-based scoring system for the detection of radiation pneumonitis in elderly patients with non-small cell lung cancer (NSCLC) or small cell lung cancer (SCLC). The receiver operating characteristic (ROC) curve is used to show the connection between sensitivity and specificity for every possible cut-off for the scoring system and select the optimal scoring point for the detection of radiation pneumonitis. The area under the ROC curve (AUC) is calculated to assess the diagnostic ability of the scoring system. Secondary objectives include positive and negative predictive values associated with each scoring point and patient satisfaction with the symptom-based scoring system (symptom-questionnaire, paper version). Based on the experiences of our previous trial and after discussion with the Ethics Committee, an assessment of quality of life was not considered necessary for the POLCAR trial [6]. It is not required for the primary objective and would mean additional stress for the patients.

### 2.2. Eligibility Criteria

The criteria for inclusion and exclusion are shown in Table 1.

### 2.3. Assessments

The following parameters will be assessed prior to radiotherapy: medical history, concomitant diseases (comorbidity), concomitant medication, physical examination, demographics, body height and weight, performance status, tumor stage and histology, upfront surgery, systemic anticancer treatment, and lung function. During the course of the study, symptoms of pneumonitis and adverse events other than pneumonitis will be assessed on an ongoing basis according to CTCAE v5.0 [16]. During the period of radiotherapy, patients are seen by medical staff members each day of radiation treatment. Following the course of radiotherapy, they are contacted weekly until the end of the study. So, it is unlikely that a patient is lost to follow-up. The timeline of the assessments is shown in Table 2.

### 2.4. Interventions

The patients receive the same radiotherapy or chemoradiation for lung cancer as they would have received without participation in the POLCAR trial. Radiotherapy is performed as volumetric-modulated arc therapy using conventional fractionation with doses per fraction of 2.0 Gy given five consecutive days per week and total doses ranging between 60 and 70 Gy [2]. The patients in this trial may receive any medical support required for adverse events, co-morbidities, or other conditions. Trial-specific interventions include completion of a paper-based questionnaire (symptom-based scoring system) once a week during and up to 24 weeks following radiotherapy and completion of a questionnaire rating the patient satisfaction with the symptom-based scoring system at the end of the radiotherapy course. The follow-up period of 24 weeks was chosen according to the results of previous studies showing that pneumonitis can occur up to 23 weeks following radiotherapy [4,5]. The English version of the questionnaire was properly translated into the languages of the participating centers.

The patients indicate and rate symptoms potentially caused by radiation pneumonitis, i.e., cough, dyspnea, and fever (Table 3), once a week by completing a paper-based questionnaire. During the radiotherapy course, the patients complete the questionnaire at the department of radiotherapy. After completion of radiotherapy, the information regarding the symptoms potentially related to pneumonitis will be obtained weekly by phone (to minimize hospital visits). The procedure of the telephone visits is clear, and uniformity is ensured. Support from caregivers is not allowed. Since the patients are contacted actively by staff members, the risk of loss to the follow-up is comparably low. In our previous trial, the rate of termination of follow-up due to the patient’s unavailability was 8.8% [6].

If the total score is higher than at baseline prior to the start of radiotherapy, the patients receive a follow-up call after 3 days or are asked to present at the corresponding hospital. If pneumonitis is suspected, the patients undergo lung function tests. The suspected diagnosis of pneumonitis is considered substantiated in case of a decrease in forced expiratory volume in 1 s (FEV1) and diffusing capacity of the lung for carbon monoxide (DLCO) to less than 75% from baseline values [16,17]. In this situation, the patients receive a chest X-Ray (which may be supplemented by a computed tomography). Radiation pneumonitis is considered confirmed if opacities confined to the irradiation fields are seen on chest X-Ray and/or ground-glass opacities (focal or nodular), consolidation, or both are seen on computed tomography [18,19]. The imaging findings are interpreted by experienced radiologists. If the diagnosis of pneumonitis grade ≥ 2 (CTCAE v5.0) is made, the patients generally receive treatment with prednisolone [5,16,20]. If the symptoms are caused by a medical condition other than pneumonitis, the patients are treated for this situation. Finally, the total score of the symptom-based scoring system is correlated to pneumonitis (yes or no). Since the scoring tool is easy to use, consistent assessment across multiple centers appears secured. This assumption is supported by the experiences from a previous prospective trial [6].

At the end of the radiotherapy course, the patients will complete a questionnaire regarding their satisfaction with the paper-based version of the scoring system, modified according to the User Experience Questionnaire, a widely used and reliable tool [21,22]. If the dissatisfaction rate is >20%, the scoring system needs to be modified, and if the dissatisfaction rate is >40%, it is considered not useful. If patients withdraw their consent to participate in the trial, study-specific interventions are stopped. In case of adverse events, which do not allow patients to complete subsequent questionnaires, study-specific interventions are postponed or discontinued, if necessary.

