#### 2.6.2. Secondary Objectives

The secondary objective is to determine positive and negative predictive values associated with each scoring point of the symptom-based scoring system. The positive predictive value is the probability that subjects with a high symptom score truly suffer from radiation pneumonitis. The negative predictive value is the probability that subjects with a low symptom score truly don’t suffer from pneumonitis. Thus, the predictive values describe the performance of the scoring system and the relevance for the subjects, whereas sensitivity and specificity describe the intrinsic validity of the test criterion. Since the incidence of subjects experiencing pneumonitis observed in this study reflects the incidence of the target population with the specific inclusion/exclusion criteria (i.e., the number of subjects with pneumonitis is not pre-specified), the positive and negative predictive values for each potential cut-off can be estimated unbiasedly. Point estimates of positive and negative predictive values will be presented.

Patient satisfaction with the symptom-based scoring system is assessed at the end of radiotherapy. Statistical analysis consists of presenting the respective proportions. In case of a dissatisfaction rate >20%, the symptom-based scoring system needs modifications before it can be used in future studies. In case of a dissatisfaction rate >40%, the scoring system will be considered not useful.

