## Figures and Tables

**Table 1 cancers-17-00807-t001:** Inclusion and exclusion criteria.

Inclusion criteria Histologically proven lung cancer Indication for radiotherapy or chemoradiation Mean radiation dose to ipsilateral lung >13 Gy Age ≥65 years Written informed consent Capacity of the patient to contract
Exclusion criteria Expected non-compliance Baseline score of >4 points, as these patients will likely not be able to tolerate the planned treatment, including the full radiation dose

**Table 2 cancers-17-00807-t002:** Schedule of enrolment, interventions, and assessments.

	Screening	Baseline	Weekly During RT	End of RT	Weekly Up to 24 Weeks After RT	End of Study
Informed consent and patient information	X					
Inclusion criteria	X					
Exclusion criteria	X					
Demographics	X					
Medical history and concomitant diseases		X	X	X	X	X
Concomitant medication		X	X	X	X	X
Systemic anticancer treatment		X	X	X	X	X
Physical examination		X				X
Telephone visits					X	
Performance status		X				
Pathology and tumor stage		X				
Upfront surgery		X				
Planned treatment		X				
Lung function test		X	X ^a^	X	X ^a^	X
Chest X-Ray and blood samples (inflammation parameters) ^b^			X ^b^	X ^b^	X ^b^	X ^b^
(Serious) adverse events			X	X	X	X
Treatment given as planned?			X	X	X	X
Symptom-based scoring system (paper version)		X	X	X	X ^c^	X
Satisfaction with the symptom-based score (paper version)				X		

RT = radiotherapy; ^a^ only in case of suspected pneumonitis; ^b^ only if the suspicions of pneumonitis are substantiated after lung function test; ^c^ by phone (telephone visit).

**Table 3 cancers-17-00807-t003:** Scoring points assigned to symptoms potentially associated with pneumonitis.

Symptom	Severity of the Symptom (as Stated by the Patients)	Points
Cough	No	0
	Yes, a little/sometimes	1
	Yes, moderate/regularly	2
	Yes, severe/permanently	3
Shortness of breath	No	0
	Yes, with intense exertion (e.g., climbing stairs)	1
	Yes, with mild exertion (e.g., walking on flat ground)	2
	Yes, at rest	3
Fever	No	0
	Yes, between 37.6 and 38.0 °C	1
	Yes, between 38.1 and 39.0 °C	2
	Yes, higher than 39.0 °C	3

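### Predictive values are called unbiased at every cut-off, but verification of pneumonitis is incomplete and depends partly on the score under test

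*Protocol article*

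**What the plan says.** **Route to diagnosis (section 2.4).** The described entry is a score above baseline: "If the total score is higher than at baseline prior to the start of radiotherapy, the patients receive a follow-up call after 3 days"; hospital attendance is the stated alternative to the call. Next, "If pneumonitis is suspected, the patients undergo lung function tests". If FEV1 and DLCO have both fallen below 75% of baseline, imaging follows, and "Radiation pneumonitis is considered confirmed if opacities confined to the irradiation fields are seen on chest X-Ray" and/or typical changes are seen on CT.

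**Schedule (Table 2).** In the two weekly columns, lung function carries the footnote "only in case of suspected pneumonitis". The entries at baseline, end of radiotherapy and end of study carry no footnote, so those tests are for everyone. Chest X-ray is conditional in every column where it appears: "only if the suspicions of pneumonitis are substantiated after lung function test".

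**Contact that does not depend on the score (section 2.3).** During the study "symptoms of pneumonitis and adverse events other than pneumonitis will be assessed on an ongoing basis according to CTCAE v5.0". Staff see patients on each treatment day and contact them weekly afterwards.

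**Analysis (section 2.6.1).** Patients with pneumonitis contribute the score at diagnosis. All others contribute their maximum score and count as non-cases.

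**Claim (section 2.6.2).** PPV and NPV for each potential cut-off "can be estimated unbiasedly", because the number of cases is not fixed in advance. "Point estimates of positive and negative predictive values will be presented".

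**The concern.** Sampling patients at their natural incidence removes one source of bias in predictive values, the artificial prevalence of a case-control sample. It does nothing about a second source: whether a patient reaches the reference standard depends partly on the index test. A patient with pneumonitis whose score does not rise is less likely to be worked up, and if not diagnosed is analysed as a non-case.

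The Introduction and Conclusions also plan to evaluate an increase from baseline. There the overlap is most direct, because a rise of at least 1 point is itself the described way into the work-up.

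The score is meant to feed a home-use application that helps decide whether a patient needs to be seen. Sensitivity and NPV are the properties that guard against false reassurance. With about 18 expected cases, one misclassified patient can decide whether a cut-off meets the plan's target.

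**Working it through.** **1. The planned numbers.** Section 2.5 states 59 patients, 18 with and 41 without pneumonitis (0.30 × 59 = 17.7; 0.70 × 59 = 41.3). With Hanley–McNeil variances, the condition is 1.960 × SE(AUC 0.7) + 0.842 × SE(AUC 0.9) ≤ 0.9 − 0.7 = 0.2. At 18 + 41 this is 1.960 × 0.0780 + 0.842 × 0.0512 = 0.153 + 0.043 = 0.196, an assurance of 82.1%. At 17 + 40 the assurance is 79.4%. The stated size reproduces and this point does not affect it. The 18/41 split is used below.

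**2. Where a missed case lands.** Let c be the cut-off and s the score recorded for a patient with undiagnosed pneumonitis.
- s < c: counted as a true negative, in truth a false negative. Observed sensitivity and NPV are too high, specificity is slightly too high, and PPV is unaffected.
- s ≥ c: counted as a false positive, in truth a true positive. Observed PPV and specificity are too low, sensitivity is too low if there are any false negatives, and NPV is unaffected.

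**3. Which applies at which cut-off.** Table 1 excludes baseline scores above 4. A patient whose score never rises therefore stays at 4 or below and is test-negative at any c ≥ 5, which includes the previous trial's cut-off of 5 (Introduction). For these patients the first case always applies. At c ≤ 4 a stable score can lie on either side of the cut-off.

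**4. Size when missed cases lie below the cut-off.** *Assumed* table: TP 17, FN 1, TN 33, FP 8. It matches 18/41 but is not in the documents, and neither is the number m of missed cases. True sensitivity = 17/(18 + m), true NPV = (33 − m)/34, true specificity = (33 − m)/(41 − m).

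| m | Sensitivity | NPV | Specificity | PPV |
|---|---|---|---|---|
| 0 | 17/18 = 94.4% | 33/34 = 97.1% | 33/41 = 80.5% | 17/25 = 68.0% |
| 1 | 17/19 = 89.5% | 32/34 = 94.1% | 32/40 = 80.0% | 68.0% |
| 2 | 17/20 = 85.0% | 31/34 = 91.2% | 31/39 = 79.5% | 68.0% |
| 4 | 17/22 = 77.3% | 29/34 = 85.3% | 29/37 = 78.4% | 68.0% |

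Section 2.6.1 sets a 90% target, read here as sensitivity. From this start one missed case breaches it. From 18/18 the result is milder: 18/19 = 94.7% with one missed case, and 18/20 = 90.0% with two, which still meets the target.

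**5. Opposite direction.** If the one missed case lies at or above the cut-off, true sensitivity is 18/19 = 94.7% against 94.4% observed, true PPV is 18/25 = 72.0% against 68.0%, and NPV stays at 97.1%.

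**6. Increase from baseline.** If a rise of at least 1 point is the usual entry to diagnosis, nearly every diagnosed case will show one, so the sensitivity of that criterion is near 100% largely by construction. A diagnosed case need not show a rise of 3 or more, the previous trial's criterion, so the argument stops at 1 point.

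**7. Sampling error.** In the assumed table the exact (Clopper–Pearson) 95% interval is 46.5–85.1% for PPV 17/25 and 84.7–99.9% for NPV 33/34.

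**The case against.** A reader might infer that patients without a score rise are never verified. Table 2 contradicts that: everyone has lung function at end of radiotherapy and end of study, with conditional imaging listed at both visits. Section 2.3 adds ongoing symptom assessment, and section 2.4 does not say that a score rise is the only ground for suspicion. This stands: verification is incomplete, not absent. It does not close the gap. The two tests are about 24 weeks apart and could miss a transient episode, and section 2.4 does not say how their results enter the case definition.

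A reader might also infer that sensitivity and NPV are upper bounds throughout. Steps 2 and 5 show otherwise. A patient whose score rises but who does not meet the lung function criterion could likewise be a missed case above the cut-off.

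Three further objections carry some weight:
- The trigger is sensitive. Any 1-point rise prompts follow-up, so many patients below a cut-off of 5 will still be followed up.
- The previous trial targeted symptomatic (grade ≥2) pneumonitis, where cases with no change in cough, breathlessness or fever should be uncommon. Section 2.4, however, relates the score to pneumonitis as yes or no, without a grade. The Discussion also accepts that undetected neurocognitive decline can distort self-report.
- Section 2.6.1 calls the cut-off preliminary and in need of validation. That softens the consequence but does not correct the claim.

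The missing intervals are minor. Section 2.6.2 does not exclude them, and the analysis plan, which is not shown, may contain them.

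**Conclusion.** The claim of unbiased predictive values is wrong as written. It rests on natural incidence alone, while the same document describes verification that depends partly on the score and is incomplete. The limitations in the Discussion do not mention this.

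The direction is settled only for missed cases whose score stays below the cut-off. That is assured for patients whose score never rises at cut-offs of 5 or more, where sensitivity and NPV are inflated. At lower cut-offs it is open. This mechanism does not inflate PPV. With no missed cases there is no bias from this source.

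The size cannot be derived from the documents. In the assumed table, the first missed case costs about 5 percentage points of sensitivity (94.4% to 89.5%) and each missed case costs 2.9 points of NPV (1/34). Whether the 90% target is lost depends on the starting table. The near-certain sensitivity of the increase criterion applies to a rise of at least 1 point only.

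**What to change.** 1. **Wording, section 2.6.2.** Replace the unbiasedness claim with a statement that the estimates assume no missed cases among incompletely verified patients. Add that at cut-offs of 5 or more, sensitivity and NPV are likely to be optimistic if cases without a score rise were missed. Note beside the increase-from-baseline results that a rise of at least 1 point is part of the route to diagnosis.
2. **Analysis.** Report the number of non-cases without reference work-up. Add a bounding analysis over an assumed range of missed cases at each cut-off, placing them below or above it as their recorded scores dictate. Give exact 95% intervals for PPV and NPV.
3. **Reconcile section 2.4 with Table 2.** State how the lung function results already scheduled for everyone at end of radiotherapy and end of study count towards case ascertainment. This asks for a clear definition and does not ask for additional imaging.

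Items 1 and 2 cost some wording and one table. Item 3 is a clarification; if it changes the protocol text, section 2.7 requires ethics committee approval. The downside is less favourable statements about sensitivity and NPV.

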### 2.6. Statistical Methods for Primary and Secondary Outcomes

#### 2.6.1. Primary Objective

The primary objective is to assess the performance characteristics of the symptom-based scoring system for the detection of radiation pneumonitis. An evaluation will be performed in patients available for assessment of the primary endpoint who have completed at least 10 questionnaires regarding their symptoms. To allow for patient-based analyses, the multiple score values documented for each patient over time will be reduced to one clinically relevant, patient-specific value only. Thus, for patients without radiation pneumonitis during the study, the maximum score value documented throughout the study will be used, and for patients with pneumonitis, we use the value documented at the time of diagnosis. These patient-specific values represent the fundamental units for all further statistical analyses. First of all, sensitivity and specificity will be estimated for every possible cut-off value of the symptom-based scoring system.

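### Section 2.6.2 calls the predictive values unbiased on sampling grounds alone, although pneumonitis is verified only in patients who pass a score and lung function gate

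*Protocol article*

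**What the plan says.** Section 2.4 describes a chain. A total score above baseline leads to a further call after three days or a hospital visit. If pneumonitis is then suspected, lung function is tested. The suspicion is "considered substantiated in case of a decrease in forced expiratory volume in 1 s (FEV1) and diffusing capacity of the lung for carbon monoxide" to less than 75% of baseline, and in that situation a chest X-ray follows, optionally with CT. Imaging settles the diagnosis: "Radiation pneumonitis is considered confirmed if opacities confined to the irradiation fields are seen on chest X-Ray", or if ground-glass opacities or consolidation are seen on CT. The score is then related to pneumonitis as a yes/no outcome.

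Table 2 repeats the gate. Imaging is done "only if the suspicions of pneumonitis are substantiated after lung function test", and this note applies at every imaging visit, including end of study. During the weekly visits lung function is tested "only in case of suspected pneumonitis"; it is also scheduled for all patients at end of radiotherapy and at end of study.

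In section 2.6.1 cases enter with the score at diagnosis, while "for patients without radiation pneumonitis during the study, the maximum score value documented throughout the study will be used". The evaluation is limited to patients available for assessment of the primary endpoint with at least ten questionnaires.

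Section 2.6.2 argues that the observed incidence mirrors that of the target population because "the number of subjects with pneumonitis is not pre-specified", and concludes that "the positive and negative predictive values for each potential cut-off can be estimated unbiasedly". Point estimates of the predictive values are planned.

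**The concern.** Unbiased predictive values need two things: a sample with the natural mix of cases and non-cases, and a correct disease status for each patient. The stated reason covers only the first. The second is not guaranteed, because imaging depends on suspicion and on two lung function criteria, and the work-up itself starts from a rise in the score being evaluated.

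A true case who never meets both criteria at any test, and who is not imaged in routine care, has no described route to a confirmed diagnosis. With a yes/no outcome, such a patient would most naturally be a non-case entered at the maximum score.

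The predictive values are a secondary objective and bear on the planned home application, which is meant to help decide whether a patient should see a pulmonologist or go to hospital. An overstated NPV would err on the reassuring side. Point estimates alone would not show any dependence on verification.

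**Working it through.** **1. The plan's own figure.** Section 2.5 gives 59 patients (18 with and 41 without pneumonitis) for AUC 0.9, lower limit 0.7, two-sided 5% and 80% assurance. I used the condition 0.9 − 0.7 ≥ 1.96·SE(0.7) + 0.84·SE(0.9) with the Hanley–McNeil variance. At 18/41, SE(0.7) = 0.078 and SE(0.9) = 0.051, which gives power of 82.1% (80.2% with the Obuchowski variance). The smallest size at the exact 7:3 ratio is 18 + 42 = 60. The figure reproduces within one patient and is not disputed.

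**2. Starting table.** Sensitivity 90% and specificity 80% are taken from the optimality definition in section 2.6.1, reading its 90% as sensitivity (an assumption).
- TP = 18 × 0.9 = 16.2; FN = 1.8
- FP = 41 × 0.2 = 8.2; TN = 32.8
- PPV = 16.2/24.4 = 0.664; NPV = 32.8/34.6 = 0.948

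**3. Direction at a fixed cut-off.** The maximum score is never below the score at diagnosis, so a missed case does one of three things:
- both scores at or above the cut-off: a TP becomes an FP
- score at diagnosis below, maximum at or above: an FN becomes an FP
- both below: an FN becomes a TN

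In none of these can PPV rise or NPV fall.

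**4. Size.** Let m cases be missed irrespective of score, with both scores on the same side of the cut-off. Then TP = 16.2 − 0.9m, FN = 1.8 − 0.1m, FP = 8.2 + 0.9m and TN = 32.8 + 0.1m. The documents give no value for m; 0 to 3 is assumed.

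| m | PPV | NPV | Specificity |
|---|---|---|---|
| 0 | 16.2/24.4 = 0.664 | 32.8/34.6 = 0.948 | 32.8/41 = 0.800 |
| 1 | 15.3/24.4 = 0.627 | 32.9/34.6 = 0.951 | 32.9/42 = 0.783 |
| 3 | 13.5/24.4 = 0.553 | 33.1/34.6 = 0.957 | 33.1/44 = 0.752 |

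As a wider range, take prevalence of exactly 30% and a missed fraction f of the cases. PPV = 0.27(1 − f)/0.41 and NPV = (0.56 + 0.03f)/0.59. For f = 0, 10, 20 and 30%, PPV is 0.659, 0.593, 0.527 and 0.461, and NPV is 0.949, 0.954, 0.959 and 0.964.

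**5. AUC.** If missed cases score like confirmed ones, the recorded AUC is (41 × 0.9 + m × 0.5)/(41 + m): 37.4/42 = 0.890 for m = 1 and 38.4/44 = 0.873 for m = 3. If low-scoring cases are missed more often, the direction can reverse. I simulated rounded normal scores (means 3.0 and 6.17, SD 1.7, clipped to 0–9, true AUC 0.90) with three missed cases and a correlation of 0.5 between score and passing the gate. The recorded AUC averaged 0.907 when the maximum equalled the score at suspicion and 0.902 when it was zero or one point higher. The sign is therefore not fixed.

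**6. What a sensitivity range must allow for.** Take cut-off 5, with 16 TP and 8 FP among the other patients, and one unimaged true case scoring 4 at suspicion, 5 at diagnosis and 5 at maximum. The true PPV is 17/25 = 0.680. As a case at the suspicion score the result is 16/24 = 0.667; as a non-case it is 16/25 = 0.640. The truth lies outside both, so the score used for a case must run from the score at suspicion to the maximum.

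**The case against.** **The coding is inferred.** No sentence says that a suspected, unimaged patient is a non-case, and the restriction to patients available for assessment of the primary endpoint could exclude those with undetermined status. This stands as a limit. A reader might infer that the protocol prescribes this miscoding; it does not. Non-case is the most natural reading of imaging confirmation with a yes/no outcome, no more.

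**The reference standard may be composite.** Suspicion, functional decline and imaging together could be the definition. A patient without the decline would then not be a missed case. The text leaves this possible, so the point is conditional on imaging-confirmed pneumonitis being the target. The wording that lung function substantiates and imaging confirms favours that reading without settling it.

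**The sentence in section 2.6.2 only contrasts a cohort with case-control sampling.** As such its premise is right, but the conclusion is worded without that limit.

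**The effect may be small.** Weekly contact, repeatable lung function, tests in all patients at two fixed visits and routine care all reduce permanent misses. With one missed case PPV moves from 66% to 63%, whereas the Wilson 95% interval for 16 of 24 score-positives is about 47% to 82%. The plan also calls its cut-off preliminary. All this stands and keeps the severity low. It does not make the unqualified statement correct.

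**Some of the remedy belongs in the SAP or case report form.** True; either may already hold it. The statement in section 2.6.2 is in the article itself.

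**Conclusion.** The unbiasedness statement is too strong. Leaving the number of cases open removes sampling bias only; unbiased predictive values also require complete verification of pneumonitis status, which the gate does not guarantee. Reading FEV1 and DLCO as alternatives would widen the gate but would not make verification complete.

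If imaging-confirmed pneumonitis is the target and unimaged cases are coded as non-cases, any error lowers PPV or leaves it, and raises NPV or leaves it. For 0 to 3 missed cases at the planned numbers, PPV runs from 0.66 to 0.55 and NPV from 0.95 to 0.96. The number missed is an assumption and may be zero.

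A reader might infer that the trial's PPV and NPV will be biased, or that the AUC is inflated or deflated. The documents support neither: they give no count of missed cases, and the AUC can move either way. The severity is minor.

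**What to change.** (a) In section 2.6.2, limit the statement to sampling, for example: *Because the number of cases is not fixed by design, the predictive values are free of bias from case sampling; unbiased estimation also requires complete verification of pneumonitis status.*

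(b) Record prospectively, and report, the number of patients with suspected pneumonitis who were not imaged.

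(c) Keep the primary analysis and the classification rule. Add a sensitivity analysis giving the minimum and maximum of PPV, NPV, sensitivity, specificity and AUC over all case/non-case assignments of these patients. As a non-case, use the maximum score; as a case, let the score run from that at suspicion to the maximum. Describe the result as a range over suspected patients only. It does not bound the values under complete verification, because never-suspected patients are also unimaged.

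I would not classify patients on routine imaging regardless of lung function. The CT criterion is not clearly confined to the irradiated field, so infections could be counted as cases, and patients would be judged by different standards.

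The cost is one recorded category, a clause and a small analysis, with no new patient procedure. Each measure is monotone in a case's score, so three options per patient suffice: six such patients give 3^6 = 729 evaluations. The price is a wider reported range. In a 150-run simulation with the scores of step 5, no correlation between score and gate, three missed cases and three unimaged true non-cases, the average ranges were AUC 0.83–0.92 (true 0.90) and, at cut-off 5, PPV 0.54–0.73 (true 0.66) and NPV 0.87–0.93 (true 0.92). If no suspected patient goes unimaged, no result changes. If the SAP already holds (b) and (c), only (a) remains.
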